#### Secondary outcomes

Secondary outcomes are paternal parenting stress, parental well-being, quality of caregiving, and infant well-being and health.

##### Paternal parenting stress

Paternal parenting stress will be measured with the same 10 items of the Dutch version of the Parenting Stress Index (PSI; [1, 18]) used for measuring maternal parenting stress. For more details, see above.

##### Parental well-being

Parental well-being is defined as: (1) depressive symptoms, (2) symptoms of anxiety, (3) satisfaction with the parental role, (4) parental self-efficacy, and (5) sleep quality and quantity.Depressive symptoms will be measured with the Edinburgh Postnatal Depression Scale (EPDS; [17]; Dutch translation Pop, Komproe, and Van Son, 1992). This scale consists of 10 items. Participants can indicate the experienced frequency of each depression-related statement on a 4-point scale. Items are scored 0, 1, 2, or 3 (items 3, 5, 6, 7,8, 9, and 10 are reverse scored). Total scores range from 0 (no depressed feelings) to 30 (severely depressed feelings). The scale shows good psychometric properties: Pop et al. [45] reported an internal consistency of .82 (Cronbach’s alpha) and sufficient concurrent validitySymptoms of anxiety will be measured with the seven items of the anxiety subscale of the Hospital Anxiety and Depression Scale (HADS; [42, 51]). For each item, participants can indicate on a 4-point scale how much anxiety they experience. Total scores on the anxiety subscale vary from 0 (no anxiety) to 21 (severe anxiety). Spinhoven et al. [51] reported good psychometric properties for the Dutch versionSatisfaction with the parental role will be measured with three items of the Dutch translation of the Parenting Stress Index (PSI; [18, 19, 36]). Following the procedure of Missler et al., [39], four items were added to this scale. Adding items was necessary because to our knowledge, no measure of parenting satisfaction currently exists. We thus decided to use this composed scale. An example item is: “I enjoy spending time with my child.” For the administration before birth (t0 and t1), the items were rephrased such that the expectation of parents of their satisfaction with their new role after the birth of their child became central: “I expect I will enjoy spending time with my child”Parents will be asked to rate their efficacy as a parent on a 5-point scale, ranging from 1 (not very good) to 5 (a very good parent; [16, 27, 49])Sleep quality and quantity is measured with two items of the Pittsburgh Sleep Quality Index (PSQI; [12]) adapted by [16]. The quality item is: “Over the last 2 weeks, how would you rate your own sleep quality?” Response options are: “Not nearly good enough”; “Not quite good enough”; “Good enough”; and “More than good enough.” The quantity item is: “Over the last 2 weeks, how would you rate your own sleep quantity?”, with the following response options: “Not nearly enough”; “Not quite enough”; “Enough”; and “More than enough.”

##### Quality of caregiving

Quality of caregiving will be measured by assessing the bonding between parent and child, the duration of breastfeeding, and the duration of room-sharing at 10 weeks postpartum.Bonding will be measured with the Maternal Postnatal Attachment Scale (MPAS; [14, 59]). This scale consists of 19 statements referring to parent-child relationship. Each statement can be answered on a 2-point; 4-point; or 5-point scale. An example item is:“When I am with the baby, I feel tense and fearful.” Total scores range from 19 to 95 and can be computed by summing up individual item scores. Low total scores indicate bonding problems between parent and child. Van Bussel et al. [59] reported a Cronbach’s alpha of .75 of the MPAS when administered 8–12 weeks after birthBreastfeeding will be assessed by measuring the duration (in weeks) of breastfeeding and/or breastfeeding mixed with bottle-feedingRoom-sharing will be measured as the duration (in weeks) of room-sharing (the infant sleeps in the room of the parents at night)

#### Infant well-being and health

The well-being of the infant will be measured through a diary (72 h at 6 weeks postpartum) assessing crying, sleeping, and feeding [6]. Parents are supposed to rate precision in 5-min slots using different symbols. The following behaviors will be assessed: asleep, awake, and being content, awake and being fussy, awake and crying, awake and feeding; awake and sucking (thumb/dummy). Parents can also indicate the time and duration of feeding, and the type of feeding (breastmilk (through breastfeeding or bottle) or formula milk). Parents are asked whether the rated 72 h period can be viewed as a “typical” period or not. Furthermore, we will ask parents at 6 and 10 weeks after birth whether they are experiencing a problem with infant sleep (day or night), crying or feeding, and if so, to rate the severity of this problem on a 7-point Likert scale ranging from 1 (hardly any problem) to 7 (a severe problem) [27]. Infant health is measured in terms of somatic indices and somatic problems (at 6 and 10 weeks after birth). Parents are asked about their infant’s weight, length, and head circumference and will also be asked to indicate whether their child has experienced fever, a runny nose, any coughing, ocular inflammation, or diaper rash. Additionally, parents are asked if their child had experienced some other medical condition and whether their child has been using any medication.

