### Statistical analysis

The study will be conducted in adherence to the Consolidated Standards of Reporting Trials (CONSORT) Statement. We will perform intention-to-treat analysis, in which all patients who are randomized will be analyzed (independent of treatment or study completion), as well as completers-only analyses. Completers are defined as participants who completed all measurements. Baseline data will be explored to see if there are differences between the group that remains in the study and the group that drops out.

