#### Primary outcome

We will compare the parenting stress scores between the two groups using a mixed multilevel model. This way, we can account for the nested structure of the data (mothers and fathers that belong to the same couple). Including both mothers and fathers in one analysis, will positively affect the power of the analyses. Furthermore, the analysis is also robust for missing data (Tabachnik and Fidell, [53]) and unequal sample sizes (more participating mothers than fathers). We will test interaction terms between parental sex (mother versus father) and intervention group (intervention versus control), to test whether the (possible) effect of the intervention is the same for both mothers and fathers. We will also calculate the between-group effect sizes at 6 (t3) and 10 weeks postpartum (t4). We will calculate Cohen’s *d* by subtracting the two mean scores and dividing them by the pooled standard deviations. A Cohen’s *d* of 0.2 can be assumed small, 0.5 to be moderate, and 0.8 to be large [13].

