#### Secondary outcomes

We will repeat the mixed multilevel models, and the calculation of Cohens’ *d*, for all outcomes of parental well-being. Next, to determine the effect of the intervention on the quality of caregiving after birth, we will add higher-quality caregiving as a secondary outcome variable to the model. Furthermore, to test whether prenatal well-being of the parents influences postpartum caregiving quality, we will use parental well-being (measured at 26 and 34 weeks of pregnancy) as a predictor of higher-quality caregiving. Finally, we will determine the effect of prenatal parental well-being on infant outcomes postpartum (mediated by higher-quality caregiving). For each of the outcomes we will calculate the between-group effect size at t3 and t4 and their 95% confidence interval. Gender will be added as an interaction term to the model, to see if there are differences between mothers and fathers.

Demographic data, attachment style of the parents and data related to the delivery and birth (birth weight, Apgar score, spontaneous delivery, caesarean section, birth complications) will be used as control variables in the model.

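### Infant problem severity exists only for parents who report a problem; the planned effect size, applied to it as collected, would compare subgroups formed after randomisation

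*Protocol article*

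**What the plan says.** In the Protocol article, Infant well-being and health, the plan for t3 and t4 is "we will ask parents at 6 and 10 weeks after birth whether they are experiencing a problem" with infant sleep, crying or feeding, "and if so, to rate the severity of this problem on a 7-point Likert scale ranging from 1 (hardly any problem"), with 7 marking the severe end. The lowest point still belongs to someone who has reported a problem, and no value is assigned to those who have not.

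In Statistical analysis, Secondary outcomes, the commitment is general: "For each of the outcomes we will calculate the between-group effect size at t3 and t4 and their 95% confidence interval". The only effect-size formula is under Statistical analysis, Primary outcome: "We will calculate Cohen’s *d* by subtracting the two mean scores and dividing them by the pooled standard deviations".

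The opening of Statistical analysis sets the analysis population: "We will perform intention-to-treat analysis, in which all patients who are randomized will be analyzed", regardless of completion. A completers-only analysis is added.

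The Discussion predicts that parents given the intervention will report fewer sleeping, crying and feeding problems.

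**The concern.** The yes/no question comes after randomisation, and the trial's own hypothesis is that the intervention shifts the answers. If that hypothesis is true, the parents who go on to rate severity are a different selection in each arm. A difference in mean severity between them then mixes two things: any change in how bad problems are, and the change in who has a problem at all. Randomisation protects the comparison of all participants, not of these two subgroups.

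Two distortions are possible. If the intervention mainly clears mild problems, those remaining are worse on average and the difference can point towards harm although nobody is worse off. If it lessens all problems alike, the effect among raters is smaller than the effect in everyone. The comparison also uses only the share of the sample that reports a problem.

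The stated robustness of the mixed model to missing data does not help. For a parent without a problem, severity is not an unobserved value to be recovered; it was never defined.

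**Working it through.** **The plan's own figure.** The only planning number is 64 per arm for the primary outcome. With d = 0.50, 80% power and two-sided alpha 0.05, the normal formula 2(1.96 + 0.842)²/0.50² gives 62.8, so 63; the t-test version gives 63.8, so 64. It reproduces, but it supplies only the arm size used below. The document gives no figure for infant problems, so **all problem rates and rating distributions below are assumptions**.

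Throughout, d = (intervention mean - control mean) / pooled SD, and negative d favours the intervention.

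**Example 1: mild problems halved.**
- Control: 40% report a problem. Among them, ratings 1 to 7 have probabilities 0.10, 0.20, 0.20, 0.20, 0.15, 0.10, 0.05.
- Intervention: problems rated 1-3 are halved and the rest are unchanged. Reporting falls to 0.40 - 0.5 × 0.40 × 0.50 = 0.30.
- Raters only: control mean 3.60 (SD 1.66). Intervention mean (1.44 - 0.22)/0.30 = 4.07 (SD 1.61). d = +0.29.
- Everyone, no problem = 0: control mean 0.40 × 3.60 = 1.44 (SD 2.05). Intervention mean 1.22 (SD 2.06). d = -0.11.
- Precision: of 64 per arm, about 26 and 19 would rate. SE(d) = √(1/26 + 1/19 + 0.286²/(2 × 45)) = 0.303, so the 95% interval is about -0.31 to 0.88.

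**Example 2: ten mild problems resolve, nobody worsens, 64 per arm.**

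| | Control | Intervention | d |
|---|---|---|---|
| Counts at ratings 1-7 | 4,6,6,5,4,2,1 (28 raters) | 0,1,5,5,4,2,1 (18 raters) | |
| Mean, raters only | 93/28 = 3.32 | 76/18 = 4.22 | 0.90/1.53 = +0.59 |
| Mean, all 64, no problem = 0 | 93/64 = 1.45 | 76/64 = 1.19 | -0.27/2.01 = -0.13 |

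Here SE(d) among raters is √(1/28 + 1/18 + 0.588²/(2 × 46)) = 0.308, and the interval is about -0.02 to 1.19.

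**When does the sign reverse?** A simulation took normal latent severity, a reporting threshold giving 20-50% reporters in the control arm, one rating point per 0.35 SD above the threshold, and 1,000,000 per arm.

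| Mechanism | d, raters only | d, everyone (no problem = 0) |
|---|---|---|
| 60% of problems rated 1-2 resolve | +0.36 to +0.38 | -0.12 to -0.13 |
| Uniform improvement of 0.2-0.5 SD | -0.09 to -0.28 | -0.13 to -0.42 |

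Reversal therefore depends on mild problems resolving selectively. A uniform improvement keeps its sign and loses about a third of its size (for example -0.16 against -0.24 with 40% reporting and a 0.3 SD shift).

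**The case against.** The strongest reply is that the article describes a questionnaire skip pattern, not an analysis. Nowhere does it say that severity is analysed as a mean among reporters or that parents answering no are left out. A statistical analysis plan could score them 0, and how a skipped item is scored is ordinary analysis-plan detail. The commitment to everyone randomised, "all patients who are randomized will be analyzed (independent of treatment or study completion"), could itself be read as implying such a rule. The sentence on effect sizes for each outcome cannot be wholly literal either, since the diary is kept only at 6 weeks. The Discussion's hypothesis of fewer problems is answered by the yes/no item, which is asked of everyone.

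Much of this stands. A reader might infer that the plan excludes parents without a problem; the document does not support that. A reader might also infer that the trial would report harm. That is not supported: reversal needs one particular pattern of benefit, the intervals in both examples include zero, and the yes/no comparison (40% against 30% in Example 1) would sit beside the severity result.

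What the reply does not remove is the misfit in the stated text. The severity item is collected at exactly t3 and t4, the times for which an effect size is promised for each outcome. The only formula given is a difference in means, and the item as defined has a value only for reporters. Nothing stated prevents the biased comparison.

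**Conclusion.** The point holds in a limited form. An effect size computed on severity as collected would condition on a post-randomisation response that the intervention is expected to change, contrary to the all-randomised principle. Whether the investigators would compute it that way is not stated.

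The size rests entirely on assumed rates and patterns. Under those, a uniform benefit is attenuated by about a third, and a benefit confined mainly to mild problems can change sign (+0.29 against -0.11; +0.59 against -0.13). With about 26 and 19 raters such a result would be misleading in direction but statistically inconclusive.

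The reach is narrow: one follow-up item in one secondary domain. The primary outcome, the 72-hour diary and the yes/no item remain valid. The change is still worth making, because these problems are a named expected benefit and the remedy costs almost nothing.

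**What to change.** State that the between-group comparison of infant problems at t3 and t4 uses all randomised participants, through one or both of:
- the yes/no problem item, reported as a proportion by arm;
- a 0-7 score with no problem scored 0, analysed by an ordinal or rank-based model for arm.

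Since both parents may rate the same infant, the model should account for two ratings per infant. Report the 1-7 severity among parents with a problem descriptively only, without a between-arm test or effect size. Fix the rule before outcomes are compared by arm.

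The cost is a scoring rule and a sentence or two of text; the yes/no answers are already collected. The drawback is that the 0-7 score will be skewed with many zeros, so Cohen's d suits it less well and the result will not be on the same scale as the other outcomes.

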#### Birth

Variables related to the delivery and the birth are assessed 2 weeks after birth: birth weight, Apgar score, spontaneous delivery, caesarean section, birth complications. We will test whether there are differences between the intervention and control groups for these variables (measuring possible stress factors during the delivery) in the analyses.

#### Marital satisfaction

Marital satisfaction is measured with the global satisfaction items of The Investment Model Scale (IMS; [48]; Dutch translation: Montgomery, Peeters, Schaufeli, and Panagopoulou, [40]). This scale consists of five items, with answering options varying from 1 (totally disagree) to 9 (totally agree). An example item is: “My relationships fulfills my needs for intimacy.” The total score ranges from 5 (not satisfied) to 45 (very satisfied). Montgomery et al., 1998, report a Cronbach’s alpha of .93. Again, we will test for potential differences on this variable between the two groups.

#### Intervention uptake

Finally, we measure the uptake of the intervention at 10 weeks after birth by asking parents whether they have read and watched the materials before the birth of their child. We also ask them whether they looked into the materials again after the birth of their child. Additionally, we monitor online the duration and frequency of watching (parts) of the video. Furthermore, we ask them to rate the frequency of using the information in their daily lives, with the item: “How many times did you use the information from the booklet, video, or the home visit during the daily care for your baby?” Response options were: “Daily”; “Several times a week”; “About once a week”; “About once every 2 weeks”; “About once a month”; “Never.” We also ask them to rate the usefulness of the booklet, video, and the home visit on a 5-point scale ranging from “Not very useful” to “Very useful.”

### Data management

We will keep one file in which research identifiers are linked to participant’s names and (e-mail) addresses. This file will be encrypted and password protected and only be available to the main researchers. All on- and offline data will be safely stored at the university using research identifier only.

### Statistical analysis

The study will be conducted in adherence to the Consolidated Standards of Reporting Trials (CONSORT) Statement. We will perform intention-to-treat analysis, in which all patients who are randomized will be analyzed (independent of treatment or study completion), as well as completers-only analyses. Completers are defined as participants who completed all measurements. Baseline data will be explored to see if there are differences between the group that remains in the study and the group that drops out.

#### Primary outcome

We will compare the parenting stress scores between the two groups using a mixed multilevel model. This way, we can account for the nested structure of the data (mothers and fathers that belong to the same couple). Including both mothers and fathers in one analysis, will positively affect the power of the analyses. Furthermore, the analysis is also robust for missing data (Tabachnik and Fidell, [53]) and unequal sample sizes (more participating mothers than fathers). We will test interaction terms between parental sex (mother versus father) and intervention group (intervention versus control), to test whether the (possible) effect of the intervention is the same for both mothers and fathers. We will also calculate the between-group effect sizes at 6 (t3) and 10 weeks postpartum (t4). We will calculate Cohen’s *d* by subtracting the two mean scores and dividing them by the pooled standard deviations. A Cohen’s *d* of 0.2 can be assumed small, 0.5 to be moderate, and 0.8 to be large [13].

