### Objectives

The primary objective of this study is to determine the postpartum effect of the intervention on maternal parenting stress. Secondary outcomes are: paternal parenting stress, parental distress in general (anxiety and depression) and parental well-being (satisfaction with the parental role, and self-efficacy in caring for the infant); quality of caregiving (bonding, breastfeeding, and co-sleeping); and infant well-being and health (crying, feeding, sleeping, well-being, and health).

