### Sample size calculation

We expect an effect size of 0.50 (Cohen’s *d*). This is based on the work of Hiscock et al. [27]. Their intervention, aimed at preventing infant sleep and crying problems, showed an odds ratio of 0.57 (converted into a Cohen’s *d* of 0.48) on symptoms of maternal depression in favor of the intervention group. Using a power of 80%, an alpha of 0.05, we need to include 64 participants in both conditions, 128 in total, to answer our primary research question.

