#### Primary outcome

The primary outcome is maternal parenting stress (assessed at t0; t1; t3; and t4) and is measured with 10 items of the Dutch version of the Parenting Stress Index (PSI; [1, 18]). The complete version of this instrument consists of 123 items. A shortened version of 25 items is available [19]. However, since the PSI has been originally developed for parents of children up to 14 years [18], our aim was to select the 10 items that are most relevant for parents of a newborn child. Following the procedure of Missler et al., [39], we selected those items that, in our view, best captured their experience. One item was added because it was considered to be central to the parenting stress construct (at least for parents with very young children): “The responsibility I have for my children weighs on me” Missler et al., [39]. An example item is: “I feel restricted by my responsibilities as a parent.” For the administration before birth (t0 and t1), the items were slightly rephrased to capture possible stress-raising expectations of parenthood: “I expect to feel restricted by my responsibilities as a parent.” Response options vary from 1 (totally disagree) to 6 (totally agree). A total score can be derived by summing the individual item scores. This total score (including the added item) ranges from 11 (no stress) to 66 (very high stress).

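### The primary analysis pools mothers and fathers and claims power for doing so, but never names the maternal contrast, which is the primary question, as the primary test

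*Protocol article*

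**What the plan says.** All references are to the protocol article.

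- **Objectives:** "The primary objective of this study is to determine the postpartum effect of the intervention on maternal parenting stress".
- **Assessments and outcomes, Primary outcome:** "The primary outcome is maternal parenting stress (assessed at t0; t1; t3; and t4").
- **Secondary outcomes (under Assessments and outcomes):** "Secondary outcomes are paternal parenting stress, parental well-being, quality of caregiving, and infant well-being and health".
- **Sample size calculation:** "We expect an effect size of 0.50" (Cohen's d), taken from an earlier trial's result "on symptoms of maternal depression in favor of the intervention group". Then: "Using a power of 80%, an alpha of 0.05, we need to include 64 participants in both conditions, 128 in total". The stated purpose is the primary research question. The abstract makes clear that the 128 are pregnant women, with partners in addition.
- **Inclusion and exclusion criteria:** partners are invited, but a woman may enter without one. The share of fathers taking part is not given.
- **Statistical analysis, Primary outcome:** parenting stress is compared between groups in one mixed multilevel model with parents nested in couples. One reason given is that "Including both mothers and fathers in one analysis, will positively affect the power of the analyses". Interaction terms between parental sex and group are tested "to test whether the (possible) effect of the intervention is the same for both mothers and fathers". Cohen's d at 6 and 10 weeks is to be calculated, without saying for which parent.

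**The concern.** The objective, the outcome definition and the sample size all concern mothers. The analysis section, under the heading for the primary outcome, describes a comparison across both parents and justifies it by power. A gain in power of the kind claimed arises when mothers and fathers share one group effect. That shared effect averages a primary and a secondary outcome, and it equals the maternal effect only if the two parents respond equally.

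Two things are at stake. If fathers respond less than mothers, the pooled test can miss a maternal effect that the trial was sized to detect. If fathers respond and mothers do not, it can be read as success on an outcome that did not move. Because no contrast is named, either the pooled or the maternal result could also be presented as primary once the data are known.

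The interaction test does not settle this. The article does not say whether the term stays in the model, which parent is the reference, or what follows from either result.

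**Working it through.** **1. The plan's own figure.** With d = 0.50, 80% power and two-sided alpha 0.05 (sidedness is not stated; one-sided would give 50 per arm), the two-sample t-test needs 63.8, so 64 per arm. Power at 64 per arm is 80.1% (t-test) or 80.7% (normal approximation). The stated 128 therefore reproduces as a comparison of 64 mothers with 64 mothers.

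**2. Inputs for the joint model.** From the article: 64 mothers per arm, 1:1 allocation, d = 0.50. Assumed, because the article does not give them: 51 fathers per arm (about 80%) and partner correlation r = 0.3. For simplicity I use unit SD, one postnatal score per parent and the normal approximation.

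**3. Variances under generalised least squares.**
- Maternal contrast: Vm = 2/64 = 0.03125, SE 0.177.
- Paternal contrast: Vf = 2[(1 − 0.09)/51 + 0.09/64] = 0.0385, SE 0.196.
- Covariance: C = 0.3 × 2/64 = 0.009375.
- Mother-father difference (the interaction): Vm + Vf − 2C = 0.0510, SE 0.226.

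**4. The common group effect.**
- Weight on mothers: (Vf − C)/0.0510 = 0.0291/0.0510 = 0.57; weight on fathers: 0.43.
- Variance: (Vm·Vf − C²)/0.0510 = 0.0219, SE 0.148.

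**5. Rejection rates, two-sided 5%.**

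| Maternal d | Paternal d | Pooled effect | Pooled test | Maternal contrast | Interaction test |
|---|---|---|---|---|---|
| 0.50 | 0.50 | 0.50 | 92% | 81% | 5% |
| 0.50 | 0.25 | 0.39 | 76% | 81% | 20% |
| 0.50 | 0 | 0.29 | 49% | 81% | 60% |
| 0 | 0.50 | 0.21 | 31% | 5% | 60% |

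**6. Break-even.** With maternal d = 0.50, pooling matches the maternal contrast when the pooled effect is 0.50 × 0.148/0.177 = 0.418. Solving 0.571 × 0.50 + 0.429 × d = 0.418 gives a paternal d of about 0.31. Above that value pooling has more power, below it less.

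**7. Pooled rejection without an interaction signal.** The pooled and interaction estimates are uncorrelated. In the last row of the table, pooled significance with a non-significant interaction therefore has probability 0.31 × (1 − 0.60) = 0.12.

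**8. What the interaction test can show.** The difference detectable with 80% power is (1.96 + 0.84) × 0.226 = 0.63 SD. A difference of 0.25 SD is found about 20% of the time.

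**9. Sensitivity.** Varying father participation over 75–100% and r over 0.2–0.6 gives pooled rejection rates of:
- 87–96% for (0.50, 0.50)
- 66–78% for (0.50, 0.25)
- 35–52% for (0.50, 0)
- 23–45% for (0, 0.50)

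**The case against.** The strongest reply is that the maternal effect can be estimated from the planned model. With sex-by-group included and mothers as the reference, the group coefficient is the maternal effect. The article does provide for that interaction, and nowhere says that it will be dropped or that the primary test comes from a model without it. A condensed article might leave the coding to a fuller document. This part stands. A reader might infer that the plan has fixed the pooled effect as its primary test, or that its error rate for mothers is 31%. The text does not support either: both need an interaction-free reading, and the 31% also leaves aside a test that the article specifies.

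The reply does not remove the mismatch. The article gives the interaction a different purpose, checking whether the effect is equal in both parents. If the term is retained and the maternal effect read off, power is about that of a mothers-only analysis, so the stated power reason no longer applies to the primary question.

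Three further points are fair:
- Pooling does not need identical effects to gain power. A paternal d above about 0.31 is enough under these assumptions.
- Zero effect in one parent is an extreme case. The article expects benefit in both, and the intermediate case loses only about 5 percentage points.
- Pooling as such is not wrong. A joint model is a sound way to handle couples.

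**Conclusion.** The point holds as an internal mismatch. The outcome, objective and sample size are maternal, while the primary analysis is justified by a power gain that belongs to a mother-father average, and the maternal contrast is never named as the test. It is not shown that the wrong test will be used.

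If the pooled effect were taken as primary, power would run from 92% (equal effects) through 76% (paternal effect half the maternal) to 49% (no paternal effect), against about 81% for the maternal contrast. An effect in fathers only would give about 31% rejections, 12% of all trials being rejections without a significant interaction. The 49% and 31% are worst cases. All these figures rest on the assumed father share, partner correlation and single postnatal score; the direction holds across the ranges examined. A non-significant interaction would not show that the parents' effects are equal, since only differences of about 0.63 SD are detected with 80% power.

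**What to change.** In the primary outcome part of the Statistical analysis section:

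1. State that the primary test is the intervention-minus-control contrast in mothers, taken either from the joint model with sex-by-group always retained or from a mothers-only model.
2. Report the paternal contrast as secondary.
3. Report the mother-father difference with its confidence interval, and do not conclude equal effects from a non-significant interaction.
4. Restrict the power sentence to the pooled effect when the parents' effects are similar.

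This changes wording only. The 128 women and 80% power then hold for the primary question, and fathers can stay in the model. What is given up is the apparent power gain from pooling. The article reports recruitment as ongoing, with 59 participants consented and nine having completed the study, so the change should be recorded before the outcome data are analysed.

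### Cohen's d for parenting stress at t3 and t4 is defined apart from the mixed model and the t0 score; it should be taken from the model

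*Protocol article*

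**What the plan says.** Under Statistical analysis, the protocol article sets the analysis population: "We will perform intention-to-treat analysis, in which all patients who are randomized will be analyzed". A completers-only analysis is planned as well.

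In the Primary outcome part of that section, the group comparison belongs to the model: "We will compare the parenting stress scores between the two groups using a mixed multilevel model". One reason given for the model is that "the analysis is also robust for missing data". Effect sizes at t3 and t4 come in addition, and Cohen's d is to be obtained "by subtracting the two mean scores and dividing them by the pooled standard deviations". Benchmarks of 0.2, 0.5 and 0.8 follow for reading it.

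The Secondary outcomes part repeats both the model and d for the parental well-being outcomes. It also promises a 95% confidence interval for the effect sizes at t3 and t4. The control variables listed there are "Demographic data, attachment style of the parents and data related to the delivery and birth"; parenting stress at t0 is not among them.

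Parenting stress is measured at t0, t1, t3 and t4 (Assessments and outcomes, Primary outcome). According to the caption of Fig. 2, the baseline questionnaire is completed before randomization.

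**The concern.** The model is chosen partly because it copes with missing scores, and it can use every randomized mother who has any score. The sentence defining d carries none of this over. It is the textbook formula for two groups of scores: two means and a pooled SD. On that reading, a mother with no score at a visit contributes nothing to d at that visit, and the t0 score is not used.

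Two consequences follow. First, d may disagree with the model's estimate for the same outcome at the same visit, with no rule for which one describes the size of the effect. Second, d is less precise than the data allow and is open to selective loss. Selective loss cannot be ruled out here: the outcome is stress, the control arm is waitlisted and participants are not blinded. The matter has some weight because d is the only effect measure the section defines visit by visit, it is the scale on which the trial was sized, and the same formula is repeated for the parental well-being outcomes.

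**Working it through.** **Inputs from the protocol article.** Planned d = 0.50, power 80%, alpha 0.05, 64 per arm (Sample size calculation); 1:1 allocation (Randomization).

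**Inputs not given, hence assumed.** The correlation rho between t0 and postpartum stress, the amount of loss and its pattern. Two-sided testing is also assumed.

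**Step 1: reproduce the plan's figure.** Normal approximation: n = 2(1.960 + 0.842)² / 0.50² = 62.8, so 63 per arm. The t-test version gives 63.77, so 64 per arm, with power 80.1%. The stated 64 reproduces and is not affected by this point.

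**Step 2: precision.** In SD units, treating the SD as known and with full follow-up at n = 64 per arm:

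- Unadjusted: SE = sqrt(2/n) = sqrt(2/64) = 0.177.
- Adjusted for t0: SE = sqrt(2(1 − rho²)/n).

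| rho (assumed) | Adjusted SE | Reduction, 1 − sqrt(1 − rho²) |
|---|---|---|
| 0.3 | 0.169 | 5% |
| 0.5 | 0.153 | 13% |
| 0.7 | 0.126 | 29% |

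**Step 3: bias when loss relates to t0 stress.** Large-sample simulation, true d = 0.50, 20% loss, logistic dropout with slope 1 on t0 stress. This applies to either postpartum visit.

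| Pattern of loss | d from observed means, rho = 0.3 / 0.5 / 0.7 | t0-adjusted |
|---|---|---|
| Completely random | 0.50 / 0.50 / 0.50 | 0.50 |
| Same rule in both arms | 0.50 / 0.50 / 0.52 | 0.50 |
| Intervention arm only | 0.55 / 0.59 / 0.63 | 0.50 |

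**Step 4: bias when loss before t4 relates to t3 stress.** Simulated trials of 64 per arm, true d = 0.50, t3–t4 correlation 0.6, t0 correlations 0.5, logistic slope 1.

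| Pattern of loss | d from observed means at 10 / 20 / 30% loss |
|---|---|
| Random in both arms | about 0.50 throughout |
| Same stress-related rule in both arms | 0.49 / 0.48 / 0.47 |
| Stress-related in controls, random in intervention | 0.45 / 0.41 / 0.36 |
| Stress-related in intervention only | 0.56 / 0.62 / 0.67 |

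An estimate using t0 and t3 averages about 0.50 in all of these. Loss in this step occurs only after t3, so it says nothing about t3.

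**Reading.** Leaving out t0 does not bias d in a randomized trial; it costs precision. Bias needs loss that differs between arms and is related to stress, and its sign depends on which arm loses its stressed mothers.

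**The case against.** The strongest reply is that the article never says the means are raw or observed. Model-estimated means would fit the same sentence, and the Secondary outcomes part names the models and d together. This stands: the reading used here is the plain one, not the only one. If model-based means are intended, one clause settles it.

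A reader might infer that the plan contradicts its own intention-to-treat statement. The article does not support that. The intention-to-treat comparison is made by the mixed model, and d is introduced as an addition. Nor does the article call d its main result. A reader might also infer that no confidence interval is planned for the primary outcome. The interval sentence stands under Secondary outcomes but speaks of each of the outcomes, so it may well cover the primary one.

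It is also fair to say that the gain from t0 may be small. The prenatal items are reworded to ask about expectations of parenthood, so the correlation with postpartum stress could be low; at 0.3 the SE falls only from 0.177 to 0.169. The larger biases belong to chosen patterns of loss for which the article gives no evidence. Both points limit the size of the concern. Neither favours an effect size detached from the model, because the model-based version uses data already collected and loses nothing when loss is harmless.

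Finally, such detail is often left to an analysis plan. Here, however, the article does fix a formula, and that formula can be improved.

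**Conclusion.** The point holds as an improvement to a supplementary effect measure. On its plain reading, the stated formula gives an unadjusted d among mothers with a score at the visit, and this can differ from the intention-to-treat model estimate. Its standard error is larger than need be: t0 adjustment would lower it by about 5 to 29% for assumed correlations of 0.3 to 0.7. It is close to unbiased (0.47 to 0.52 for a true 0.50) when loss is random or similar in both arms. It is off in either direction (0.36 to 0.45, or 0.55 to 0.67) when loss is stress-related in one arm only, at assumed losses of 10 to 30%.

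All of these ranges rest on assumed correlations and dropout patterns. The model-based estimate stays near 0.50 because loss in these scenarios depends only on scores already observed; loss driven by unobserved stress at the visit itself could bias either estimate. The finding does not show a breach of intention to treat, an error in the primary test or a fault in the sample size arithmetic checked here.

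**What to change.** In the Primary outcome and Secondary outcomes parts of Statistical analysis:

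- Define d at t3 and at t4 as the t0-adjusted group difference estimated from the intention-to-treat mixed model, divided by one SD named in advance. Use mothers for the primary outcome and report fathers separately.
- Name the SD and keep it the same throughout. The pooled t0 SD does not depend on postpartum loss but rests on items worded as expectations. The pooled SD at the visit is on the postpartum scale but comes from the mothers who remain.
- State the 95% confidence interval for the primary outcome explicitly, derived from the model difference.
- Label any d computed from observed means as descriptive. Observed means and SDs can stay in a table.

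The cost is analysis wording only. The t0 score is already collected, and no visit, questionnaire or sample size changes.
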